#### Falls questionnaire (T1, T2)

This questionnaire, answered by the participant, serves to find out whether she/he experienced any falls during the intervention. The participant states whether falls required medical attention, what kind of treatment was needed and by whom it was provided.

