### Aims

Our research questions are:
Compared to controls, does volunteer-supported walking improve physical function and quality of life as well as lower fear of falling? Furthermore, improves supported walking the cognitive executive function and the general physical activity? [Effectiveness]Compared to controls, does volunteer-support walking increase the rate of falls needing medical attention, rate of admissions to hospital, duration of hospitalisations and mortality? [Safety]Compared to controls, does supported walking have an impact on the frequency and duration of hospitalisations and/or mortality? [effectiveness, safety]

Finally, we explore whether the intervention can be successfully implemented into existing community services.

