### Study procedure and intervention

After baseline assessments (T0) and randomisation, individuals in the intervention group will participate in a supported physical activity intervention for 6 months. They will be visited by an assigned volunteer three times a week to go for a walk outdoors. The duration of the walk will depend on the participant’s physical ability. The aim is to gradually increase walking duration to three times 50 min to meet the WHO recommendation of 150 min per week [6]. In case of bad weather, the activity can take place indoors and will consist of exercises for balance and strength based on a programme of the federal centre for health education [15]. Each participant and his/her volunteer together will keep an activity diary, noting the date, time, duration and type of each activation exercise (outdoors or indoors). Events relevant for safety, e.g. falls or injuries, will also be recorded. Furthermore, after each walk, the subjectively experienced physical strain of the walk will document by a visual analogue scale.

Participants in the control group are invited to two lectures covering topics related healthy ageing during the 6 months of the intervention. The presentations will be in an easy to understand and entertaining manner and address health related topics for older people, e.g. nutrition. After 6 months of intervention the post intervention examination will take place (T1). We will evaluate the effect of the intervention in comparison with the control group. Study participants in both groups will be followed for another 6 months until the 12 months final examination (T2). During this period, the study centres will neither provide nor coordinate any walking service. However, we expect the collaborating partners and other community services to continue providing support for regular walking as initiated during the first 6 months of the study.

The evaluation of the extended period at T2 has two main objectives. First, to prolong participants’ follow-up and to assess long-term effects of regular walking (up to 12 months) and second, to evaluate potential sustainability and dissemination of the study intervention after cessation of support from the study centres (Fig. 1).

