#### Treated falls (T1, T2)

This questionnaire documents, whether the participant experienced any medically treated falls during the intervention. The medical staff states the date and diagnosis and whether the fall occurred during the intervention.

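### Both fall forms are given at T2 but described as covering only the intervention, which ends at T1; taken literally, falls in months 7-12 are not asked about

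*Protocol article*

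**What the plan says.** All references are to the protocol article.

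- **Falls questionnaire (T1, T2).** The participant answers a form that "serves to find out whether she/he experienced any falls during the intervention". The answers listed are whether a fall needed medical attention, what treatment was given and who gave it. No fall date is listed.
- **Treated falls (T1, T2).** The purpose is given as: "This questionnaire documents, whether the participant experienced any medically treated falls during the intervention". Then: "The medical staff states the date and diagnosis and whether the fall occurred during the intervention".
- **Table 1.** Falls and treated falls are both marked at T1 and at T2, with no restriction to one arm. The treated-falls row includes the date.
- **Study procedure and intervention.** After T0, "individuals in the intervention group will participate in a supported physical activity intervention for 6 months". Both groups are then followed for six further months to T2. Of that second half the section says: "During this period, the study centres will neither provide nor coordinate any walking service".
- **Aims.** The safety question is comparative: "does volunteer-support walking increase the rate of falls needing medical attention", alongside hospital admissions, length of stay and mortality.
- **Data analysis.** Falls requiring medical attention are to be compared by a χ2, Fisher exact or log-rank test, and a mediator analysis of falling is planned. Exploratory subgroup analyses of the primary and secondary outcomes are to be run at both T1 and T2.

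**The concern.** A form completed at month 12 should cover the time since the previous visit. Both fall forms are instead tied to a period that closed six months before T2. If they are used as described, the T2 visit asks again about months 1-6 and asks nothing about months 7-12.

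Those later months matter to the trial's own aims. The article gives long-term effects as one purpose of T2, and it expects partner organisations and community services to go on supporting walks after T1. Falls in that period bear on the safety question. Falls that were never asked about may not be reliably recovered later.

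The second worry is the meaning of the phrase. If some respondents take it as the six-month period and others as the supported walk itself, the item can be answered differently by arm. Neither participants nor study personnel are blinded, so nothing in the procedure would prevent this.

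**Working it through.** **The plan's own figures.** The article gives no rate, power or sample size for falls. Its only sample-size figure concerns SPPB at T1, and it reproduces. The residual SD is 2.8 × √(1 − 0.5) = 1.980. With 103 per group the non-centrality is 206 × 0.50² / 1.980² ≈ 13.1, and the F test on 1 and 203 degrees of freedom has 95.03% power. Inflating for 40% loss gives 206 / 0.6 = 343.3, so 344 with equal groups, against 345 stated. None of this bears on falls; the point rests on wording.

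**Step 1: windows side by side.**

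| Visit | Period since last visit | Window as described | Months of that period covered |
|---|---|---|---|
| T1 | months 1-6 | the intervention (months 1-6) | 6 of 6 |
| T2 | months 7-12 | the intervention (months 1-6) | 0 of 6 |

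The uncovered share of follow-up is 6 / 12 = 50%.

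**Step 2: can recorded dates repair this?** Only in part. The treated-falls form records a date, so a fall from months 1-6 reported again at T2 can be recognised and not counted twice. A date cannot supply a fall that the form did not ask about. The participant questionnaire lists no date, so a repeat report at T2 could not be separated from a new one.

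**Step 3: is the wording only loose shorthand?** The physical activity record, described just before the falls questionnaire and also used at T1 and T2, has a calendar window: the past 14 days. It applies equally to either arm and either visit. The fall instruments have no such window.

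**Step 4: the two uses in the treated-falls form.** The first use defines which falls are documented. The second is an item that medical staff answer about the fall. If both mean the six-month period, the second adds nothing. If the second means the supported walk, it is informative, but a control can never answer yes. The article does not say which is meant.

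**Step 5: illustration of what half the follow-up is worth.** All inputs except group size are assumptions: 172 per arm (345 / 2, rounded down), no losses, control six-month risk p of a treated fall, risk ratio 1.5, and the same risks in each half-year independently. Twelve-month risks are 1 − (1 − p)² for controls and 1 − (1 − 1.5p)² for intervention. Power is for a two-sided 5% comparison of two proportions, normal approximation.

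| Assumed p | Power, months 1-6 only | Power, all 12 months |
|---|---|---|
| 5% | 16% | 27% |
| 10% | 29% | 48% |
| 15% | 43% | 67% |
| 20% | 57% | 80% |

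The comparison assumes that the effect on falls persists after T1, which the article does not establish. It shows only that the lost half-year could matter.

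**The case against.** The strongest reply is that this is a condensed article. The sentences state what the forms are for; they are not the item text, and the forms are not shown. Both are scheduled at T2, and T2 exists partly to prolong follow-up. The authors may well intend falls since T1 and have written one sentence with T1 in mind. This stands as a limit on certainty: the real forms may be sound. It does not remove the conflict, because the window the article states cannot be applied at T2.

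A reader might go further and infer that controls have no intervention period at all, so that their fall count is zero by construction and the arms are measured on different bases. The documents do not support that. The article applies the period to controls: "Participants in the control group are invited to two lectures covering topics related healthy ageing during the 6 months of the intervention". On that reading both arms are asked about the same months at T1. Table 1, the Aims and the Data analysis section all presuppose falls counted in both arms. Only the last item of the treated-falls form plausibly means a supported walk.

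A reader might also infer that the diary inflates the intervention arm's falls. The diary is kept with the volunteer and does record falls, and no control diary is described. But the article names the diary as a source for physical activity only and does not say that its falls enter the endpoint. Prompted recall is possible, not documented.

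**Conclusion.** The point holds as a conflict of wording with a practical consequence. As described, the T2 fall forms cover 0 of the 6 months since T1, while the schedule and the planned T2 analyses need those months. The ambiguity in the treated-falls form adds a risk of unequal capture between arms.

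It would go too far to say that the 12-month fall outcome will be empty, or that months 1-6 will be counted twice. The first follows only if the actual forms carry the literal window. The second is limited by the date on the treated-falls form and remains open only for the undated participant questionnaire.

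Severity is moderate. Treated falls are one of several secondary and safety outcomes, and the primary analysis of SPPB at T1 does not use them. No size or direction of bias can be given, because the article states no fall rates; the power figures above are assumption-driven.

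**What to change.** 1. Give both forms one calendar window, identical in both arms: T0 to T1 at the T1 visit, and T1 to T2 at the T2 visit.
2. Add the fall date to the participant questionnaire, as the treated-falls form already has it.
3. If the last item on the treated-falls form means a supported walk, word it as a fall during a volunteer-supported session. Use it to describe the intervention arm only and keep it out of the between-arm comparison.
4. State in the analysis section that the between-arm fall comparison uses only sources collected the same way in both arms, and report diary falls descriptively.

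The cost is rewording two forms and adding a sentence to the analysis section, with no extra visits or staff. If the forms in use already carry a since-last-visit window, correcting the description and clarifying the session item is enough.

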#### Treated falls (T1, T2)

This questionnaire documents, whether the participant experienced any medically treated falls during the intervention. The medical staff states the date and diagnosis and whether the fall occurred during the intervention.

### Outcomes

We expect the intervention to impact upon muscle strength, balance and ability to walk. We therefore chose the Short Physical Performance Battery as the main outcome of the study. SPPB scores have been shown to be associated with disability in mobility and activities of daily living [26–28], future hospitalisation [29], health improvement [30] and mortality [30–32]. For these simple measures of performance, the SPPB shows a good reliability and validity [27].

As secondary outcomes we will evaluate quality of life (EQ-5D-5L), fear of falling (FES-I), physical activity (activity diary), cognitive executive function (clock drawing test), falls requiring medical attention, hospitalisation and death.

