**Methods/design:**

In a randomised, controlled interventional superiority-trial, individuals older than 65 years of age living in the community or nursing homes will be randomised into two groups. The study will be conducted in two study centres with assessments at baseline, 6 and 12 months. The intervention group will participate in a supported physical activity intervention for 6 months. An assigned volunteer will visit them three times a week for an outdoor walk between 30 and 50 min, or equivalent indoor activity. Persons in the control group will be invited to two lectures covering topics related to health. Primary endpoint is the physical function measured by the Short Physical Performance Battery (SPPB) at baseline, after 6 and 12 months. Secondary and safety endpoints will be quality of life (EQ. 5D), fear of falling (Falls Efficacy Scale), physical activity (activity diary), cognitive executive function (clock drawing test), falls requiring medical attention, hospitalisation and death. Primary analysis will be carried out by intention to treat.

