#### Physical activity record (T1, T2)

The participant states the number and duration of walks during the past 14 days and whether she/he walked together with a volunteer or somebody else.

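### The secondary outcome physical activity is tied to a diary described only for the intervention arm; the 14-day walk record, not limited to one arm, should be named instead

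*Protocol article*

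**What the plan says.** The Outcomes section names an instrument for each patient-reported or tested secondary outcome: "quality of life (EQ-5D-5L), fear of falling (FES-I), physical activity (activity diary), cognitive executive function (clock drawing test"). The Methods paragraph of the Abstract repeats the pairing: "physical activity (activity diary), cognitive executive function (clock drawing test), falls requiring medical attention, hospitalisation and death".

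The diary itself is described under Study procedure and intervention, in the paragraph on the intervention group: "Each participant and his/her volunteer together will keep an activity diary, noting the date, time, duration and type of each activation exercise". That paragraph says of the intervention participants: "They will be visited by an assigned volunteer three times a week to go for a walk outdoors". The next paragraph turns to the other arm: "Participants in the control group are invited to two lectures covering topics related healthy ageing during the 6 months of the intervention". It mentions neither a volunteer nor a diary.

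A second activity instrument has its own heading, Physical activity record (T1, T2): "The participant states the number and duration of walks during the past 14 days". It also asks whether the walk was taken with a volunteer or with someone else. Table 1 carries what is evidently the same item as a Walk Assessment row in the participant block. It is marked at T1 and T2 but not at T0, and Table 1 has no row for the diary.

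The research question, posed against controls, is whether "improves supported walking the cognitive executive function and the general physical activity". The Data analysis section applies ANCOVA, t-tests or Mann-Whitney tests to secondary outcomes. It also plans a mediator analysis of falls, on the ground that falling depends on fear of falling and on how active the person is.

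**The concern.** A between-arm outcome needs an instrument applied in the same way in both arms. The diary as described fails this in two ways. Controls have no volunteer with whom to keep it. What it records is the delivery of the intervention, not what participants do overall.

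If an analyst followed the outcome list literally, controls would be missing or, worse, scored as zero. A difference would then arise from the way the data were collected, even if intervention participants did nothing beyond the supported sessions. The same difficulty would carry into the falls analysis if the diary supplied the activity mediator, because a mediator observed in one arm only cannot be modelled.

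There is also a pre-specification issue. The outcome list names one instrument and the assessment schedule another, and the two would give different answers. In a trial where study personnel know the allocation, that choice should be settled in advance.

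**Working it through.** **1. Can the diary support the comparison?** The places in the protocol article, side by side:

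| Place | Instrument | Arm | Time | Content |
|---|---|---|---|---|
| Abstract; Outcomes | activity diary | not stated | not stated | physical activity |
| Study procedure and intervention | activity diary | intervention paragraph; kept with the volunteer | 6-month intervention | date, time, duration and type of each session |
| Table 1; Physical activity record | 14-day walk record | no restriction | T1, T2 | number and duration of walks, accompaniment |
| Aims | none named | contrast with controls | not stated | general physical activity |
| Data analysis (falls mediator) | none named | both arms needed | not stated | amount of physical activity |

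The instrument in the first two rows exists, as described, in one arm. The questions in the last two rows need both arms. Only the third row meets that need, and the outcome list does not mention it. After T1 the study centres no longer provide walks, and no diary is described for that period, so the diary as described does not cover T2 either.

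**2. Size if the diary were used as labelled.**

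- Controls without a diary value: 345 / 2 = 172.5, so about 172 at 1:1 allocation, before any loss to follow-up.
- Intervention minutes at full adherence, with three sessions a week of 30 to 50 minutes (Abstract): 3 × 30 = 90 and 3 × 50 = 150 minutes a week.
- At the adherence floor of the per-protocol analysis, 25% of scheduled walks: 0.25 × 90 = 22.5 and 0.25 × 150 = 37.5 minutes a week.

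The built-in difference against a control value scored as zero could thus be about 22 to 150 minutes a week, depending on delivery. No such scoring is specified; the range shows what the label would produce if blanks were read as no activity.

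**3. What the 14-day record would contain at T1.** The recall window can cover the last two weeks of the intervention. At full adherence with all sessions outdoors, volunteer walks would contribute 2 × 90 = 180 to 2 × 150 = 300 minutes to the total. Total walking and walking without a volunteer therefore answer different questions, and the accompaniment item allows both to be reported.

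**4. Effect on the plan's own figures.** The sample size concerns the primary outcome. With a 1-point difference, SD 2.8, R-square 0.5, two-sided 5% and 95% power:

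n per group = 2 × (1.960 + 1.645)² × 2.8² × (1 − 0.5) / 1² = 101.9, so 102.

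The noncentral F calculation gives 95.03% power at 103 per group, which matches the stated 103. Allowing for 40% loss, 206 / 0.60 = 343.3, so 344 against the stated 345. These figures reproduce, and nothing in this point changes them.

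**The case against.** The strongest reply is that this is a naming slip. The assessment schedule already contains a participant-reported walk record, taken at T1 and T2 and not confined to one arm, so data for a between-arm comparison are planned. That stands. A reader might infer from the diary label that physical activity cannot be compared between arms at all; the documents do not support that. The limitation belongs to the diary.

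Three further inferences also go too far:

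- **A missing baseline invalidates the analysis.** The record is not taken at T0, so baseline-adjusted ANCOVA is unavailable. But the Data analysis section also allows t-tests and Mann-Whitney tests. In a randomised trial an unadjusted comparison at follow-up is valid, only less precise.
- **The diary will hold 90 to 150 minutes a week.** That is a full-adherence target. The article says duration depends on ability and is built up gradually, and its per-protocol rule anticipates participants with fewer than a quarter of the walks.
- **Controls are stated to keep no diary.** The article does not say so. It is a strong inference from a diary kept jointly with a volunteer and described in the intervention paragraph.

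It can also be said that total walking, supported walks included, is a legitimate outcome, because supported walks may replace walks participants would have taken anyway. That is fair, and it is a reason to report total walking alongside unaccompanied walking, not instead of it.

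What the reply does not remove is the conflict itself. The instrument is stated twice, in the Abstract and in Outcomes, and both times it is the one that cannot serve the stated comparison. This is a statement in the article that is wrong as written, not a detail left to an analysis plan.

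**Conclusion.** The point holds as a wrongly named instrument. As written, the secondary outcome physical activity is an adherence measure in one arm. It can support neither the contrast with controls posed in Aims nor the activity mediator for falls. The data needed for a between-arm comparison of walking are already scheduled under a different name.

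The conclusion rests on two readings: that controls keep no diary, which is inferred, and that the 14-day record is taken in both arms, which follows from the absence of any restriction in Table 1 and in its own section. The record has limits that should be acknowledged. It covers walks only, which is narrower than general physical activity; it is self-reported in an unblinded trial; and it has no T0 value.

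Severity is moderate. One secondary outcome and the mediator analysis of falls are affected. The primary endpoint, its analysis and the sample size are not.

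**What to change.** 1. In the Abstract and in Outcomes, replace the activity diary as the instrument for physical activity with the physical activity record. Define the outcome as the number of walks and minutes walked in the past 14 days, at T1 and T2, in both arms.
2. Report total walking and walking not accompanied by a volunteer separately, using the accompaniment item already collected.
3. State that the activity mediator in the falls analysis comes from the same record.
4. Keep the diary for adherence and for the safety events noted in it.

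These are wording changes that use data already scheduled, so the cost is close to nil.

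Optionally, take the record at T0 as well for participants not yet enrolled, so that the comparison can be adjusted for baseline. This gains precision and is not needed for validity. It costs one short extra form per participant, and those already enrolled would lack the T0 value.
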